**Statistical analysis:**

*Phase I: Feasibility and toxicity.* Patients will receive concurrent treatment with extracranial radiosurgery and Sutent. Both the radiation dose and Sutent dose will be escalated as the trial progresses from Levels 1 through 5 as shown in Table 1. The starting radiation dose is 40 Gy in 10 fractions and the starting Sutent dose is 25 mg PO QD. The dose escalation strategy is as follows: The trial will start with dose level 1. At each level, 3 patients will be treated and their toxicities will be assessed. If no patients experience dose limiting toxicity, the trial will proceed to the next dose level. If 1 patient develops unexpected acute toxicity at any dose level, an additional 3 patients will be treated at that dose level. If ≥2 patients experience unexpected toxicity, the previous dose level will be declared the maximal tolerated dose for Phase II evaluation

*Phase II (Includes 3 to 6 patients from Phase I MTD):* The median progression free survival with optimal chemotherapy alone for the 4 most common tumor types (lung, breast, prostate and colorectal) ranges from 2.2 to 10.6 months, depending on primary tumor site and degree of pretreatment. Therefore, we will assume a median time to progression of 6.4 months (standard deviation 3.2 months) with chemotherapy alone. Using the data from this trial, response rates will be estimated and Kaplan-Meier curves generated for progression-free and overall survival (1). With 38 patients for the phase II portion, this study has 87% power (α=0.05) to detect a 25% increase in time to progression. Also the 2 year freedom from progression is <5% with chemotherapy therapy and this study has 70% power (α=0.05) to demonstrate a 10% absolute increase in 2 year progression-free survival.

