**2. INTRODUCTION/BACKGROUND**

2a. Rationale for New Approaches to Metastatic Cancer

Cancer is the second leading cause of death in the United States, predominantly due to inability to control progressive metastatic disease (2). Save for notable exceptions such as germ cell tumors, drug therapy alone is not curative therapy for patients with solid tumors with gross disease (3). However, not all patients with metastatic cancer succumb to their disease. Surgery and chemotherapy has resulted in long-term disease free survival in approximately 25% of patients with colorectal cancer and isolated liver metastases (4). Additionally, some patients with isolated pulmonary metastases, most notably soft tissue sarcoma, are rendered disease-free with resection and chemotherapy (5). These data lend support to the notion that not all metastases are diffuse and some patients may limited, organ specific metastases (6).

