Spread of the primary tumor to regional lymph nodes or distant organs is common in patients with cancer. The evolution of clinical metastasis is based in part on the anatomic proximity of the primary tumor to the lymphatic and vascular supply and drainage. Examples include the spread of epidermoid cancers of the lung, head and neck and cervix to draining regional lymph nodes and gastrointestinal cancers to the liver through the portal system. Historically several hypotheses based on clinical evidence attempted to explain mechanisms of metastatic tumor cell spread. Halsted suggested that tumor cells spread in an orderly manner initially spreading to regional lymph nodes and then centrifugally to distant organs (7). In contrast, the “systemic hypothesis” first suggested by Keynes and most clearly articulated by Fisher proposes two principal types of cancer: those that cannot metastasize and those that have metastasized widely before clinical detection (8, 9). In an attempt to reconcile clinical and laboratory features in a unified hypothesis, the “spectrum” model has been proposed by Hellman (10). This theory accepts that some tumors have spread widely before clinical detectability while others never metastasize, but for the majority of cancers, metastatic capacity evolves during the clinical phase of tumor growth. In this model, metastatic proclivity evolves during tumor growth. During this evolutionary process, there may be a stage, termed “oligometastases,” when metastases are limited in number and location because metastatic capacity has not fully evolved (6). If this hypothesis is valid, these patients would benefit from effective local therapy in addition to systemic therapy.

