**Study Proposal and Rationale**

Patients with metastatic cancer are generally treated with chemotherapy, which has improved median survival compared to best supportive care. Despite this, patients continue to have persistent disease at sites that were initially involved with cancer.

Radiation therapy is an effective modality for treating localized cancer but until recently has been only used for palliation of symptoms once a patient develops metastatic disease. However, there is a rapidly enlarging clinical experience of extracranial stereotactic radiation to aggressively treat metastatic sites. Since patients with metastatic disease clearly have systemic disease, there is an urgent need to integrate effective drug therapy with increasingly effective local therapy. Although, both extracranial stereotactic radiation and Sutent have favorable toxicity profiles, there are no clinical data on the combination. The goal of the phase I trial is to use increasing doses of extracranial stereotactic radiation therapy to all sites of involved disease in combination with increasing doses of Sutent in order to determine the dose limiting toxicity (DLT), and maximum tolerated dose (MTD). The goal of the phase II trial is to determine if the addition of radiation therapy and Sutent will improve progression-free survival and overall survival and at the minimum have a positive impact on quality of life, response rate and palliation of symptoms.

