**4.** **INCLUSION CRITERIA**

1. Histologically or cytologically confirmed diagnosis of cancer (including epithelial carcinoma, sarcoma, and melanoma)
2. Age 18 years or older
3. Life expectancy > 3 months
4. Patients with AJCC (6th edition, 2002) stage IV cancer with distant metastases and without pleural or pericardial effusion at diagnosis and before start of study
   1. Patients with pleural effusion that is transudative, cytologically negative,

and non-bloody are eligible

- 1. If a pleural effusion is too small for diagnostic thoracentesis, the patient will be eligible.

1. Patients with 1-5 sites of maximum tumor dimension (for each individual site) of ≤ 10 cm or < 500 cc volume and amenable to radiation therapy as seen on standard imaging (CT, MRI, bone scan, PET/CT)
2. Unidimensionally measurable disease (based on RECIST) is desirable but not strictly required.
3. Brain metastases must have been treated prior to enrollment on study, preferably with stereotactic radiosurgery or surgery.
4. Eastern Cooperative Oncology Group (ECOG) performance status ≤ 2 (Karnofsky ≥ 60%)
5. No prior radiation therapy to currently involved tumor sites
6. Room air saturation (SaO2) > 90%
7. Patients must have normal organ and marrow function as defined below:

Hemoglobin > 9.0 g/dl

Absolute neutrophil count (ANC)  1,500/l

Platelets  100,000/l

Total bilirubin within institutional limits

Albumin > 2.9 g/dl

Alkaline phosphatase < 2.5x upper limit of normal

AST and ALT <2.5 x upper limit of normal

1. Informed consent must be obtained from all patients prior to beginning therapy. Patients should have the ability to understand and the willingness to sign a written informed consent document.
2. Inclusion of Women and Minorities: Both men and women of all ethnic groups are eligible for this trial. The proposed study population is in the table below:

Table 2:

|  | White, not of Hispanic origin | Black, not of Hispanic origin | Hispanic | Asian or Pacific Islander | Unknown | Total |
| --- | --- | --- | --- | --- | --- | --- |
| Male | 24 | 4 | 6 | 2 | 0 | 36 |
| Female | 20 | 3 | 5 | 1 | 0 | 29 |
| Total | 44 | 7 | 11 | 3 | 0 | 65 |

1. Radiation therapy requirements: Patient must have a completed treatment plan approved by the protocol review team ([name] or [name] AND [name] or [name])

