**16. STATISTICAL CONSIDERATIONS**

- Phase I: The primary objectives are to determine the maximum tolerated dose (MTD) and dose limiting toxicity (DLT) of extracranial stereotactic radiation therapy in combination with Sutent when given to all sites of involved disease in patients with metastatic cancer.
- For dose escalation purposes, the major endpoint will be dose-limiting toxicity occurring within 30 days after the start of radiation therapy.
- Dose limiting toxicity is defined as follows: Grade 3-5 non-hematological toxicities (excluding nausea, vomiting, and alopecia) and Grade 4-5 hematological toxicities.
  - Esophagitis and mucositis are very common side effects with radiation therapy and grade 3 side effects can be seen after palliative courses of radiotherapy. Therefore, grade 3 mucositis or esophagitis lasting ≤ 7 days will not be considered a DLT. If the grade 3 mucositis or esophagitis lasts > 7 days, it will then be considered a DLT.
- The MTD for a specific area will be exceeded if 2 or more patients out of 6 (or a third or more) with disease at that site experience DLT at that dose. The dose immediately below will be recommended for further study.
- Phase II: *(Includes 3 to 6 patients from Phase I MTD):* The median progression free survival with optimal chemotherapy alone for the 4 most common tumor types (lung, breast, prostate and colorectal) ranges from 2.2 to 10.6 months, depending on primary tumor site and degree of pretreatment. Therefore, we will assume a median time to progression of 6.4 months (standard deviation 3.2 months) with chemotherapy alone. With 38 patients, this study has 87% power (α=0.05) to detect a 25% increase in time to progression. Also the 2 year freedom from progression is <5% with chemotherapy therapy and this study has 70% power (α=0.05) to demonstrate a 10% absolute increase in 2 year progression-free survival.
  - All patients included in the study will be assessed for response to treatment, even if there are major protocol treatment deviations or if they are ineligible (intent-to-treat population). Criteria described in Section 10 will be used to assign each patient to one of the following response categories: 1) complete response, 2) partial response, 3) stable disease, 4) progressive disease, 5) early death from malignant disease, 6) early death from toxicity, 7) early death because of other cause, or 8) unknown (not assessable, insufficient data).

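### The 70% power for 2-year PFS holds only against a 5% reference for metastatic cancer in general, and the protocol does not justify that rate for the patients with 1-5 sites whom it enrols

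*Protocol*

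**What the plan says.** The phase II paragraph of Section 16, repeated in the synopsis under Statistical analysis, first gives a range of chemotherapy-alone medians for the four most common tumour types and adopts one benchmark: "we will assume a median time to progression of 6.4 months (standard deviation 3.2 months) with chemotherapy alone". It then adds a second sizing statement, that "the 2 year freedom from progression is <5% with chemotherapy therapy and this study has 70% power", at α=0.05, "to demonstrate a 10% absolute increase in 2 year progression-free survival". No source is cited for the <5%, and neither place limits it by number or size of metastases.

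The enrolled population is narrower. Section 4 admits "Patients with 1-5 sites of maximum tumor dimension" within a stated size limit. Section 2a describes the oligometastatic stage as one in which "metastases are limited in number and location because metastatic capacity has not fully evolved". Section 16 also lists the number of lesion sites at baseline as a potential prognostic variable.

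Phase II has no control arm. Even so, the Study Proposal and Rationale gives its goal as to "determine if the addition of radiation therapy and Sutent will improve progression-free survival and overall survival".

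**The concern.** In a single-arm trial, any statement that treatment improved PFS rests on the reference rate. Here that rate describes chemotherapy-treated metastatic cancer at large, while the patients are selected for limited disease. The protocol's rationale depends on such patients being different. If they would do better than 5% at 2 years without the study regimen, a result above 5% could reflect selection alone and still be reported as a demonstrated gain from radiation plus Sutent. The stated power would also be too favourable for the question asked, because detecting a 10-point gain over a higher reference with 38 patients is harder.

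**Working it through.** **Inputs from the protocol (Section 16 and synopsis):** n = 38; reference p0 = 5% (the upper end of <5%); target p1 = 5% + 10 points = 15%; α = 0.05, sidedness not stated; stated power 70%.

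**Step 1: reproduce the 70%.**

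- Exact binomial, one-sided. The smallest count r with P(X ≥ r | 38, 0.05) ≤ 0.05 is r = 5. P(X ≥ 5 | 0.05) = 0.040 and P(X ≥ 5 | 0.15) = 0.693. Power is 69.3%.
- Normal approximation, two-sided. The standard errors are √(0.05×0.95/38) = 0.0354 under the null and √(0.15×0.85/38) = 0.0579 under the alternative. Power = Φ[(0.10 − 1.96×0.0354)/0.0579] = Φ(0.530) = 70.2%.

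Both agree with the stated figure, so there is no arithmetic error.

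**Step 2: how far the 5% null can be wrong.** Solving P(X ≥ 5 | 38, p) = 0.05 gives p ≈ 5.3%. Above that control rate, the exact test built on 5% no longer holds one-sided 5% error.

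**Step 3: other control rates.** The protocol gives no 2-year rate for patients with 1-5 sites on chemotherapy alone, so the rates below are assumptions. The third column is the chance of 5 or more of 38 with no treatment effect. The last columns reset the count to the smallest with exact one-sided error ≤ 5% and give power for a true 10-point gain over that rate.

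| Reference rate | Status | P(X ≥ 5), no effect | Reset count (error) | Power for +10 points |
|---|---|---|---|---|
| 5% | protocol | 4.0% | 5/38 (4.0%) | 69% |
| 7.4% | assumed | 15% | 7/38 (2.0%) | 50% |
| 10% | assumed | 33% | 8/38 (3.2%) | 50% |
| 15% | assumed | 69% | 10/38 (4.9%) | 49% |
| 20.8% | assumed | 92% | 13/38 (3.9%) | 38% |

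The 7.4% and 20.8% are what exponential curves with medians of 6.4 and 10.6 months would give at 24 months: 0.5^(24/6.4) = 0.074 and 0.5^(24/10.6) = 0.208. They serve only as illustrative points, for the reason given under the objection.

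Part of the fall in power is discreteness. At 7.4%, a count of 6/38 would have error 5.9% and power 67%. All rows assume that 2-year status is known for all 38 patients. The 5/38 count is derived here to reproduce the 70%; the protocol states no such decision rule.

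**The case against.** The strongest reply is that nothing in the protocol shows the <5% to be wrong for these patients. No control rate for patients with 1-5 sites is given. Section 2a reports that half the patients in one metastatic lung chemotherapy trial had three or fewer sites, so chemotherapy populations overlap with the enrolled group. Eligibility also admits any histology, prior chemotherapy and, in Section 4, performance status up to 2, all of which could lower the control rate. Taking 5% from <5% already uses its least favourable end. Section 16 plans Kaplan-Meier estimation, and imperfect matching to a historical benchmark is common to single-arm phase II trials.

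Much of this stands. The size of the distortion is unknown, and below about 5.3% there is none in the error rate. What remains is that the rate is unsourced, makes no allowance for the selection on which the rationale rests, and supports a goal worded as improvement due to the added treatment.

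Several stronger readings are tempting and should not be drawn:

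- **That <5% contradicts the 6.4-month benchmark.** The 7.4% needs an exponential curve, whose SD with that median is 6.4/ln 2 = 9.2 months. The protocol states an SD of 3.2. A lognormal with median 6.4 and SD 3.2 leaves about 0.1% progression-free at 2 years, which is compatible with <5%.
- **That only a one-sided test gives 70%, or that two-sided power is really 51%.** The 51% is the exact power with a count of 6/38. The two-sided normal approximation gives 70.2%.
- **That the background supplies a control rate of 25%.** The figure of "long-term disease free survival in approximately 25% of patients with colorectal cancer and isolated liver metastases" follows surgery and chemotherapy in one selected group. It is not a chemotherapy-alone rate.
- **That the reference should simply be 7.4% with a count of 7/38.** That rate comes from the same unrestricted benchmark and carries no information about limited disease.

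**Conclusion.** The concern holds as a problem with the reference rate and the conclusion drawn from it, not with the arithmetic. The 70% is correct for 5% versus 15% with 38 patients and for no other reference. Whether error and power fail in practice depends on a control rate that the protocol does not give. If it exceeds about 5.3%, an exact test built on 5% has more than 5% error. Over the assumed range of 7.4% to 20.8%, that error runs from 15% to 92%, and power at a valid one-sided 5% falls to between 50% and 38%. A reader might infer that the error rate and power are known to be wrong. The document does not support that; it shows only that they are unsupported for the enrolled population, and that its own rationale points towards a rate above the unrestricted one.

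**What to change.** Change the 2-year sentence in Section 16 and in the synopsis. State that the 70% power holds only against a 5% reference, and that exceeding 5% does not by itself show that radiation plus Sutent improves PFS in patients with limited metastases. Then do one of two things:

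- justify, with a source, a 2-year reference rate for patients with 1-5 sites and restate the power at 38 patients; or
- make the comparison descriptive, reporting the Kaplan-Meier 2-year PFS with a confidence interval and a short table of error and power for reference rates of 5-25%.

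The cost is a wording change and a small table, with a less favourable stated power and a weaker claim. No extra patients or procedures are needed.

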**17. CONFIDENTIALITY**

Study records that identify patients will be kept confidential. Study records will contain patients’ name, address, and medical history number and will be available to the study doctor, research nurse, and data coordinator. Data collected in this study will be maintained on a password protected computer that only the primary investigator, co-investigators, research nurse, and data coordinator will be able to access. Study records will be secured in locked offices in the department of radiation oncology. Neither patients’ name nor other personally identifying information will be used in any publication resulting from the research study.

**APPENDIX II**PERFORMANCE STATUS SCALES

**ZUBROD PERFORMANCE SCALE**

0 Fully active, able to carry on all predisease activities without restriction *(Karnofsky 90-100)*.

1 Restricted in physically strenuous activity but ambulatory and able to carry out work of a light or sedentary nature. For example, light housework, office work *(Karnofsky 70-80)*.

2 Ambulatory and capable of all self-care but unable to carry out any work activities. Up and about more than 50% of waking hours *(Karnofsky 50-60)*.

3 Capable of only limited self-care, confined to bed or chair 50% or more of waking hours *(Karnofsky 30-40)*.

4 Completely disabled. Cannot carry on any self-care. Totally confined to bed or chair *(Karnofsky 10-20)*.

### **Appendix 3.** **Mount Sinai Department of Radiation Oncology Clinical Trials Data and Safety Monitoring Plan**

### **I. Clinical Trials Monitoring Committee**

The Clinical Trials Monitoring Committee is responsible for continued review and monitoring of all clinical trials conducted by the Mount Sinai Department of Radiation Oncology. This committee provides oversight of study progress and safety by review of accrual and adverse events at quarterly meetings. The Committee:

#### a) Reviews all clinical trials conducted at the Mount Sinai Department of Radiation Oncology for progress and safety.

#### b) Reviews all adverse events requiring expedited reporting as defined in the protocol.

#### c) Reviews reports generated by the Mount Sinai Department of Radiation Oncology data quality control review process (internal audit, quality assurance review, and response review) described in Section II of this document.

#### d) Submits recommendations for corrective actions to the Institutional Review Board.

#### e) Notifies the Study Chair of the recommended action.

#### f) Notifies external sites participating in multiple-institutional clinical trials coordinated by the Mount Sinai Department of Radiation Oncology of expedited adverse events and/or committee recommendations.

Members are appointed by the Director of the Mount Sinai Cancer Center Clinical Trials Office. Membership duration is flexible to maintain required depth and breadth of expertise related to the spectrum of clinical research conducted at the Cancer Center. Interim meetings are scheduled to address specific issues that require immediate attention to insure patient safety.

Membership

| Name | Discipline |
| --- | --- |
| [name]. | Medical Oncology |
| [name]. | Radiation Oncology |
| [name]. | Urology |
| [name]., M.S. | Radiation Oncology |
| [name]. | Medical Oncology |
| [name]. | Patient Advocacy |
| [name]. | Radiation Oncology |

## A. Data and Safety Monitoring Plan

### 1. Requirements

All clinical trials conducted at the Cancer Center must have a satisfactory data and safety monitoring plan that is described in detail in the protocol. The Clinical Trials Monitoring Committee review insures patient safety and that the degree and frequency of data and safety monitoring for individual studies will be commensurate with the size, complexity and risks of the trial.

### 2. Elements of a Data and Safety Monitoring Plan

#### a) Delineation of oversight responsibilities (either external DSMB or Mount Sinai Department of Radiation Oncology Clinical Trials Monitoring Committee).

#### b) Description of data and safety review process.

#### c) Time table for submission of data, safety, and progress information to the DSMB or Clinical Trials Monitoring Committee, the IRB, and the sponsor.

#### d) Process to implement closure of studies when significant risks or benefits are identified.

#### e) Description of adverse event reporting procedures.

## B. Guidelines for Data and Safety Monitoring Implementation

### 1. Monitoring and Reporting Requirements

Mount Sinai Department of Radiation Oncology monitoring requirements for trials without an acceptable external DSMB are as follows:

#### a) Phase I Trials

#### Investigators will conduct continuous review of data and patient safety at their biweekly Clinical Trials Quality Assuarance meetings where the results of each patient’s treatment are discussed and the discussion is documented in the minutes. The discussion will include for each dose level: the number of patients, significant toxicities as described in the protocol, dose adjustments, and responses observed. Quarterly summaries will be submitted to the Clinical Trials Monitoring Committee for review.

#### b) Phase I/II and Phase II Trials

#### Data related to these trials are discussed at regularly scheduled Clinical Trials Quality Assuarance meetings where the results of each patient’s treatment are discussed and the discussion is documented in the minutes. The discussion will include for each treatment arm/dose level: the number of patients, significant toxicities as described in the protocol, dose adjustments, and responses observed. Twice yearly, summaries will be submitted to the Clinical Trials Monitoring Committee for review.

